# 1 Protocol Summary

## 1.1 Synopsis

| **Title:** | TranExamic Atomized for Pediatric post-Operative Tonsillectomy hemorrhage: A Pilot and Feasiblity Study |  |  |  |
| --- | --- | --- | --- | --- |
| **Study Description:** | This study starts as single site pilot study, randomized, double-blinded controlled trial for 12 patients. Then dependent on funding, the study will be a multi-center, randomized, double-blinded, placebo-controlled trial. It is a parallel arms pilot trial randomizing up to 30 patients. |  |  |  |
| **Objectives:** | \| Primary Objective: \| The primary objectives of this pilot study are:   1. Enroll 0.6 patient's/site/month with PTH and 2. Evaluate the ability to nebulize at least two doses of TXA to children with PTH and 3. Determine the indirect local and systematic concentrations of nebulized TXA in children 4. Adverse events will be assessed 30 +/- 5 days from randomization \| \| \| \| --- \| --- \| --- \| --- \| \| Secondary Objectives: \| The secondary objectives of this pilot study are:   1. Determine the number and rationale for PTH patients to return to the OR; and 2. Determine the number of blood transfusions and estimated blood loss and 3. Determine the recurrence of PTH after TXA, saline or return to the OR. \| \| \| \| Exploratory Objectives: \| \| Establish pain and anxiety inventory at 7 +/- 1 from randomization. \| | | |  |
| **Endpoints:** | \| Primary Endpoint: \| Enrollment after one year, % of nebulization administered to patient's enrolled, and collection of two blood samples from each participant. Adverse events will be assessed at 30 +/- 5 days from randomization. \| \| --- \| --- \| \| Secondary Endpoints: \| Collection of surveys on ENT decision to go to the OR, electronic health record data on blood transfusions and estimated blood loss, and if PTH recurrences within seven days of randomization. \| \| Exploratory Endpoints: \| Age-appropriate pain and anxiety states at 7 +/- 1 days after randomization. \| | | | |
| **Study Population:** | Children aged 2 to 17 years old that present with post-tonsillectomy hemorrhage (PTH), ENT clinicians, parents of the children enrolled and missed eligible. | |  |  |
| **Phase:** | 2 | |  |  |
| **Description of Sites/Facilities Enrolling Participants:** | The University of Texas Health Science Center/University Health System for single site study then will expand to University of California at Davis, and Hasbro Children Hospital/Brown University School of Medicine | |  |  |
| **Description of Study Intervention:** | After randomization, children will receive three TXA nebulization doses (500 mg each) or three saline nebulized doses (placebo). | |  |  |
| **Study Duration:** | Study 1: 12 months, Study 2: 12 to 18 months | |  |  |
| **Participant Duration:** | Thirty days after randomization | |  |  |

## 1.2 Schema

[figure not shown]

**Figure 1: Schema of TEAPOT Pilot**

Our overall study objective is to reduce the need for surgical control of post-tonsillectomy hemorrhage (PTH). Our primary objective for this pilot trial is enroll at least 0.6 patients/site/month and deliver at least two of three nebulization of TXA. The schema of our pilot trial will provide important data to improve the design of a larger Phase 3 trial.  Feasibility goals of the pilot trial include assessment of the consent process, the number of nebulization delivered to enrolled patients, and determine local and systematic concentrations of nebulized tranexamic acid (TXA) using a verified pulmonary physiologically based pharmacokinetic model. Data from the pilot trial will then help to inform a Phase 3 study design with an optimal consent process, pragmatic protocol, and dose selection of nebulized TXA to reduce the need for surgical control of PTH.

## 1.3 Schedule of Activities (SoA)

| **Procedure** | **Day 0-1***  **Enrollment** | **Day 7 +/- 1** | **Day 30 +/- 5 End of Study** |
| --- | --- | --- | --- |
| Screening and eligibility | X |  |  |
| Medical history | X |  |  |
| Consent | X |  |  |
| Demographics/baseline information | X |  |  |
| Concomitant medication review | X | X |  |
| ED/Hospital admission data collection** | X | X |  |
| Randomize to “use next box” | X |  |  |
| Administer study nebulization 1 | X |  |  |
| Administer study nebulization 2 | X |  |  |
| Administer study nebulization 3 | X |  |  |
| Surgical hemorrhage control (Y/N) | X | X |  |
| 1st TXA Level (last neb up to 60 mins) | X |  |  |
| 2nd TXA Level (60 mins to 8 hours) *** | X |  |  |
| ENT OR decision survey | X |  |  |
| Process, freeze, store, and ship samples | X |  |  |
| Age-appropriate Pain Scale |  | X |  |
| Parents and Children (Promis Anxiety Scale 8a) |  | X |  |
| Adverse and serious adverse events | X | X | X |

*Randomization to 24 hours

**Should include the following, if collected per standard of care: vital signs (including height and weight), physical exam, ENT upper airway exam, lab data collection (coagulation labs, other routine lab tests), OR use, ENT exam & findings as relating to OR use (e.g., photo of tonsillar bed), blood product usage, final hospital disposition. At seven days, further, evaluate if participants had been readmitted for bleeding after an intervention.

***Time points must be separated by 60 to 90 minutes.

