Systemic administration of TXA achieves hemostasis both intra- and post-operatively in orthopedic, dental, cardiovascular, and trauma literature (19, 20). Systematic reviews document that intravenous TXA may be effective when administered prophylactically or perioperatively to prevent primary PTH but not secondary PTH (21). Additionally, large retrospective studies document that high-dose intravenous TXA can have significant delayed-onset adverse events, including seizures, thromboembolism, renal insufficiency, and changes in vision (17). Given the potential risks associated with systemic TXA administration, oral inhalation of TXA may have fewer side effects and be more effective. Studies document that inhaled drug formulations compared to intravenous increase airway and upper GI tract tissue exposure (22). Schwarz *et al.* was the first to report a case of a three-year-old boy to receive nebulized TXA who presented on postoperative day three with a PTH (23). The patient did return to the operating room, but the bleeding had stopped on arrival thus no operative intervention was needed. In 2021, we published a retrospective cohort documenting that three doses of nebulized tranexamic acid delivered for PTH in children appear to be safe and beneficial. This study documented a 44% reduction in the need for a second operation (24). Compared to earlier reports and studies, nebulized TXA is the first non-operative intervention that successfully decreased the need for an invasive procedure to control upper airway bleeding in children with PTH. This study was supported with a larger retrospective study of 83 patients treated, documenting a significant decrease in the need for operative control and repeat bleeding (25). Shin *et al* reported that TXA-treated patients had a decreased rate of operating room intervention of 36.1% versus 60.2% (p<0.0001) and a rate of repeat bleeding of 4.9% versus 14.2% (p<0.02). The odds ratio for operating room intervention with TXA treatment was 0.37 (95% CI 0.22, 0.63). There were no adverse effects identified with an average follow-up time of 586 days.

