# 3 Objectives and Endpoints

| OBJECTIVES | ENDPOINTS | JUSTIFICATION FOR ENDPOINTS |
| --- | --- | --- |
| Primary | | |
| Evaluate the feasibility to enroll 0.6 patients/site/month  Nebulize at least two of three doses of TXA to children with PTH.  Determine the local and systematic concentrations of nebulized TXA in children  Determine incidence of adverse and serious adverse events | Enrollment after one year and % of nebulization’s. Go/no-go threshold is 0.6 patients per site per month for a total of 22 patients. Time and success to obtain consent will establish need for exception for informed consent (EFIC).    The goal is >90% of patients will receive at least two of three planned nebulization of TXA.  Collection of two blood samples from each participant. This will verify a pulmonary physiological-based PK model (PBPK) (i.e., nasal cavity, pharynx, and lung) that indirectly predicts the oropharyngeal and systematic concentration of nebulized TXA.  A phone call or email will be placed to participants at 30 +/- 5 days. | The overall incidence of PTH is 5%, yet numbers per site may be very different. Assessment and consent will optimize site selection, recruitment process, and the plan the main trial.    The establishment of a pragmatic protocol design will help design a large trial.  Limited data on nebulized TXA systematic absorption. Topical PK studies of TXA document a significant reduction in systematic levels but the same hemostasis effect.  Safety Evaluation as recommended by the FDA. |
| Secondary | | |
| Determine the number and rationale for PTH patients to return to the OR; and    Determine the number of blood transfusions and estimated blood loss and      Determine the recurrence of PTH after TXA, saline, or return to the OR. | Collection number participants and surveys on ENT surgeons’ decision to go to the OR    Collection of electronic health record data on number of blood transfusions and estimated blood loss    Survey families to determine PTH recurred seven days from randomization. | To evaluate if return to the OR can be an outcome for the main trial.    To evaluate if TXA decreased severity of PTH bleeding.      To evaluate if TXA or return to OR prevented PTH recurrence. |
| Tertiary/Exploratory | | |

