## 7.3 Lost to Follow-Up

A participant will be considered lost to follow-up if we are unable to measure the secondary outcomes up to seven to thirty days from randomization including the need for surgical intervention (Y/N) or additional bleeding. At least 3 attempts will be made to follow up with the participants using contact information provided during the consent process.

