# 8 Study Assessments and Procedures

## 8.1 Efficacy Assessments

The **primary feasibility outcomes** for the pilot trial are the enrollment rate (patients per site per month) and the proportion of patients receiving study drugs (at least 2 nebulized doses).  Safety is always an outcome, and all adverse events will be reviewed.

**The secondary outcome is** the ENT surgeon rationale, decision (Y/N) for the PTH patient to return to the OR, severity of bleeding with estimates of blood loss that include volume of hemorrhage recorded blood loss, and the number of blood transfusions. Additionally, we will determine the indirect local and systematic concentration of nebulized TXA by verifying our pulmonary physiologically based pharmacokinetic model. To verify the model, two lab samples will collect at opportunistic times either by finger stick or ad**. The study is not** powered for the secondary outcomes as this a pilot trial.

The **exploratory outcomes** will be age-appropriate pain scores and parent and child anxiety scales as measured by anxiety-state-trait scale (STAI). For children under eight years old their anxiety will be measured by STAI-C, which utilized pictures These will be exploratory as the pilot trial is not powered to determine the change in the outcomes.  Please see **Figure 7** for a timeline of all study procedures and outcomes.

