# 9 Statistical Considerations

## 9.1 Statistical Hypotheses

The pilot study is not designed to test an efficacy hypothesis, but rather to determine the feasibility for patient enrollment and the number of doses received per patient.

**Our primary hypothesis** for the single site and the multi-site study is that we can enroll at least 0.6 patients per site per month and deliver a minimum of two out of three planned nebulized TXA doses to >90% of enrolled patients.  The single site study will only be one year and the multi-site study for 18 months. We will test each of this (yes/no) hypothesis using a Mantel Haenszel test stratified by site for a total of 12 patients for the single-site study for greater than 24 nebulization and for the multi-site study up to 22 patients with greater than 44 nebulization's recorded as delivered.

**Our secondary goals** will be to determine if nebulized TXA prevents going to the OR for PTH and utilization of blood products. These goals are not powered to be tested in the pilot study. **Our second aim** is to verify a pulmonary physiological based pharmacokinetic (PBPK) model (i.e., nasal cavity, pharynx, and lungs) will predict the change in the area under the curve (AUC0-α) of TXA concentration in systemic compartments with accuracy (average absolute fold error <2) and precision (average fold error <2). We will calculate the AUC of accuracy and precision of the model using the linear trapezoid rule. For the PBPK model, we will use previously published PK data to construct the model before verifying it with systematic samples.

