### 9.4.2 Analysis of the Primary Efficacy Endpoint(s)

Differences between TXA and saline conditions with respect to the primary outcome (i.e., need for surgical intervention: yes or no) will be analyzed statistically using the Mantel Haenszel test stratified by site.

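### The surgical outcome is worded as return to the OR, as surgical control, and as a blend of the two, and no section says how to code a child taken to the OR who needs no hemostatic procedure

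*Protocol*

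**What the plan says.** The protocol words its clinical outcome in three ways.

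- **Return to the OR.** A secondary objective in Section 3 is "Determine the number and rationale for PTH patients to return to the OR", and its stated justification is "To evaluate if return to the OR can be an outcome for the main trial". The synopsis (1.1) carries the same objective. Section 9.1 sets a goal to "determine if nebulized TXA prevents going to the OR for PTH and utilization of blood products". Section 8.1 lists the surgeon's "decision (Y/N) for the PTH patient to return to the OR".
- **Surgical control or intervention.** The item in Section 1.3 is "Surgical hemorrhage control (Y/N"), marked at Day 0-1 and Day 7 and repeated in the responsibilities table of Section 6.4. Section 7.3 defines loss to follow-up partly by "the need for surgical intervention (Y/N) or additional bleeding". Section 9.4.2 applies a Mantel-Haenszel test stratified by site to the "primary outcome (i.e., need for surgical intervention: yes or no").
- **A blend.** Section 2.3.2 describes going back to the OR for hemostasis within 24 hours. Section 8.2.4 describes returning to the OR for surgical management, followed for seven days. Section 9.2 introduces its 76% as children going to the OR for surgical control, then calls the fall to 61% a fall in surgical care.

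Section 2.2 reports a child given nebulized TXA for whom the two events part: "The patient did return to the operating room, but the bleeding had stopped on arrival thus no operative intervention was needed".

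**The concern.** Entering the OR and having a hemostatic procedure there are different events. Section 2.1 describes the usual OR visit as examination under general anesthesia plus cautery, so an examination without cautery is a foreseeable result. The protocol gives no rule for it.

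The distinction bears on what the pilot is for. Section 3 says this endpoint is collected to judge whether return to the OR can serve as the main-trial outcome. A pilot that records a differently worded event under its dedicated item cannot answer that cleanly. The claimed benefits also attach to different events: less anesthesia exposure (Sections 2.2 and 2.3.2) follows from not entering the OR, while hemostatic efficacy is shown by whether a procedure was needed. The event rate and the choice of outcome handed to phase 3 are what is at stake.

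**Working it through.** **Step 1. Code the Section 2.2 child under each wording.**

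- Return to the OR (1.1, 3, 9.1): yes.
- Surgical hemorrhage control or surgical intervention (1.3, 6.4, 7.3, 9.4.2): no.
- OR return for hemostasis or surgical management (2.3.2, 8.2.4): unclear. The child went for that purpose but did not receive it.

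Section 4.2 describes what appears to be the same report (a three-year-old given nebulized TXA) as operative management prevented. The protocol's own narrative thus counts as favorable a child who is a yes under the Section 3 endpoint.

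**Step 2. Can both events be recovered from other planned data?**

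- The Section 1.3 footnote includes OR use and ENT findings related to it, at Day 0-1 and Day 7, but only where collected as standard of care. Section 8.2.2 repeats that condition for exam findings.
- The physician survey in Section 8.2.2 asks for the reasoning and the OR examination, if one was done. It is voluntary and anonymous and goes out within 24 hours of randomization. Section 1.3 schedules the ENT decision survey at Day 0-1 only, so it does not cover OR visits later in the seven-day window.

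So both events can probably be derived for most children, but this is not assured, and nothing fixes which one Section 9.4.2 compares.

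**Step 3. Reproduce the phase 3 figure.** Inputs from Section 9.2: p1 = 0.76, p2 = 0.61, one-sided alpha = 0.025, power 80%, Fisher's exact test, 324 children. Equal arms are assumed.

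- Mean proportion = (0.76 + 0.61)/2 = 0.685.
- n per arm = [1.960 × √(2 × 0.685 × 0.315) + 0.842 × √(0.76 × 0.24 + 0.61 × 0.39)]² / 0.15² = 149.4, rounded up to 150.
- With continuity correction: (149.4/4) × [1 + √(1 + 4/(149.4 × 0.15))]² = 162.4, rounded up to 163, or 326 in total.
- Exact unstratified Fisher power at 162 per arm (324 in total) is 0.801.

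The stated 324 reproduces, so the arithmetic is sound.

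**Step 4. Illustrate how far it depends on the event.** Let f be the share of OR returns with no hemostatic procedure. The protocol gives no f, so these values are assumptions. Suppose also that 76% and 61% count all OR returns, which Section 9.2 leaves open. The surgical-control rate in each arm is then the OR-return rate × (1 − f).

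| f, control / TXA | Rates, control vs TXA | Total N, continuity-corrected | Exact power at 324 |
|---|---|---|---|
| 0 / 0 | 76.0% vs 61.0% | 326 | 0.80 |
| 5% / 5% | 72.2% vs 58.0% | 378 | 0.74 |
| 10% / 10% | 68.4% vs 54.9% | 436 | 0.66 |
| 20% / 20% | 60.8% vs 48.8% | 572 | 0.54 |
| 10% / 20% | 68.4% vs 48.8% | 216 | 0.94 |

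The required N rises if f is equal in both arms. In the last row, where TXA doubles f, it falls. Even the direction therefore depends on a quantity the pilot could record but does not fix.

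**The case against.** The strongest reply is that these are loose synonyms for one composite event. The blended wording in Sections 2.3.2, 8.2.4 and 9.2 supports that. So does the chart data on OR use and ENT findings, from which an exam-only child could usually be identified. Coding rules may also sit in the manual of operations, to which Sections 6.4 and 8.2.2-level data detail are partly deferred, and that manual is not shown. The pilot is not powered for this outcome (8.1, 9.4.1), and its go/no-go threshold is enrollment (3, 9.2). All of this limits the consequence. It does not supply a rule for the uncoded child or say which event Section 9.4.2 tests.

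A reader might infer four stronger things that the documents do not support.

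- *That there are two cleanly rival endpoints.* The blended sections rule out so sharp a split. What exists is inconsistent wording with one uncoded case.
- *That the classification is lost, or that sites will certainly code differently.* Other planned data probably allow recovery, and site practice is unknown.
- *That one reclassified child shows the size of the problem.* With 6 per arm (Section 5.5), one child moves an arm's rate by 1/6 = 16.7 points, against a planned phase 3 difference of 76% − 61% = 15 points. But that is true of any single event in a six-child arm, so it does not measure this defect.
- *That a surgeon's decision later cancelled forms a third endpoint.* Section 8.1 lists the decision beside the surgeon's rationale, which fits the separate ENT survey. Nothing shows it was meant as a separate outcome.

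**Conclusion.** The point holds in limited form. The outcome is worded as OR return, as surgical control and as a blend. The protocol's own case report is coded differently under the first two, and no section resolves it. Both events can probably, but not reliably, be derived from data collected where standard care provides them.

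Enrollment, the go/no-go decision and the arithmetic behind 324 are unaffected. The harm is confined to the event rate and outcome definition passed to phase 3, and to the meaning of the Section 9.4.2 comparison. Its size cannot be given, because the frequency of exam-only OR visits is not stated. The range of 216 to 572 rests wholly on assumed shares and on reading 76% and 61% as all OR returns. It shows sensitivity and does not estimate an error in the plan. The change is still worth making before enrollment, since it bears directly on the aim stated in Section 3 and costs very little.

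**What to change.** 1. In Sections 1.3 and 6.4, replace the single item with two required fields: (a) entered the OR for PTH, Y/N, with date and time; (b) hemostatic procedure performed, Y/N.
2. Tabulate both by arm.
3. Have the sponsor name one of them as the event and use the same words in Sections 3, 8.1, 8.2.4 and 9.4.2, bringing 1.1, 7.3 and 9.1 into line. Which one is the sponsor's choice: Section 3 points to OR return, while the overall objective in Section 1.2 points to surgical control.
4. Reconcile the window (24 hours in 2.3.2, seven days in 8.2.4) and the status (primary in 2.3.2 and 9.4.2, secondary in 3, 8.1 and 8.2.4).
5. State in Section 9.2 which event the 76% and 61% describe.

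The cost is two chart-abstracted fields and wording changes. No new procedure or contact with families is needed.

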# 2 Introduction

## 2.1 Study Rationale

Tonsillectomy is the second most performed surgical procedure on children in the United States, with more than 530,000 performed annually^1^. Four to five percent of children return to emergency departments (ED) for post-tonsillectomy hemorrhage (PTH)^2^ . This usually results in hospital readmission, blood transfusions, and/or surgical interventions^1,3^. To control PTH, more than 75% of pediatric otolaryngologists choose to go to the operating room for examination under general anesthesia and cauterize the bleeding source^4^. Non-operative management of PTH is challenging because visualization and application of direct pressure will obstruct breathing. Interventions such as gargles, silver nitrate, or topical hemostatic agents do not decrease the need for surgical hemostasis^5^. Development of a topical hemostatic agent for PTH remains challenging because of the extensive tonsillar vascular supply, constant exposure to saliva and bacteria, and shear forces from swallowing and coughing that detach the material from the tonsillar surface^6^.

The ideal treatment for PTH would be a drug that is effective, safe, and inexpensive. Tranexamic acid (TXA) is an antifibrinolytic drug, that competitively inhibits plasmin, part of the body’s natural process to degrade clots (Figure 3). Intravenous and topical TXA reduces blood loss for various types of pediatric surgery, without an increase in adverse events^7,8^. Nebulized TXA has also been shown to reduce bleeding in children with hemoptysis or pulmonary hemorrage^9^. In addition, a case report has documented that single dose of nebulized TXA given to a child with PTH may prevent the need for surgical hemostatic control^10^.  To confirm and extend these results, we completed a preliminary study evaluating nebulized TXA in 58 children with PTH. Three consecutive doses of nebulized TXA were given to 14 children at 500 mg per dose for children >25 kg and 250 mg per dose for children <25 kg. Our single-arm study demonstrated that nebulized TXA significantly decreased the surgical control of PTH by 44% compared to historical controls. There was no associated increase in adverse events or delays to surgery.

[figure not shown]

**Figure 2. Proposed mechanism of action of nebulized tranexamic acid (TXA) in post-tonsillectomy hemorrhage.** The left panel illustrates nebulized TXA delivery to the oropharynx. The center panel depicts the tonsillar fossa following tonsillectomy. The right panel illustrates the proposed antifibrinolytic mechanism whereby TXA competitively inhibits plasminogen activation and reduces fibrin clot degradation. The conceptual illustrations were generated using ChatGPT (OpenAI) based on author-developed scientific content and were subsequently reviewed, edited, and approved by the authors.

Children with PTH typically do not receive hemostatic interventions in the ED while awaiting the otolaryngologist’s arrival. In addition, many children with PTH present to hospitals that do not have immediate access to pediatric otolaryngology and thus require transport to tertiary hospitals. Nebulized TXA has the potential to be an easy, efficient, and safe ED intervention to stabilize potentially life-threatening bleeding from PTH and decrease the need for surgical interventions. Nebulized TXA likely has less side effects because the effect is topical, and little should be absorbed systemically. However, there are no studies that determine the local systematic absorption. Using known data from other studies and small number of systematic samples we can construct and verify a model that will determine the local and systematic absorption of nebulized TXA.

